#### Statistical analyses

Data will be assessed using SPSS software (version 20; SPSS Inc., Chicago, IL, USA). Correctness of the data will be assured by double-entry of the data. Data will be analyzed according to both intention-to-treat (ITT) and per-protocol (PP; efficacy population) principles. ITT will assess all randomized patients, while PP analyses will assess patients who receive 2 weeks of morning light therapy with no violation of the study protocol.

All planned comparisons will compare T2 to T5 relative to T1. The primary endpoint of the study is change in depressive symptoms (BDI-II total score) during the trial. Baseline depression level (that is, BDI-II total score at T1) will be controlled for in the two-factor repeated-measures ANCOVA. This model accounts for differences between groups at baseline. Furthermore, the study will evaluate whether the effects of morning light therapy on mood might partly be mediated by its effect on the circadian rhythm, and will be assessed by questionnaires and saliva samples. For missing values, the multiple imputations (MI) technique will be used, because a recent meta-analysis for RCTs in obesity found this to have modest superiority to fitting mixed linear models or using last observation carried forward (LOCF) methods [76]. With the MI technique, plausible values for the missing data are imputed. Each of the datasets is then analyzed separately using the desired model (in this case, the two-factor repeated-measures ANCOVA). With this parameter, estimates are made for each of the datasets, and these are then combined using standard rules for MI analyses [77,78]. These combined parameter estimates can then be used for hypothesis testing and for making inferences. In this RCT, two-factor repeated-measures ANCOVA will be used with group as between-subject factor and time as within-subject factor (T1 to T5). In cases of significant correlations with the primary endpoint, covariates will include baseline BDI-II score, gender, intelligence, seasonality, and circadian preference. The 95% confidence intervals and pre-post effect sizes will be derived for each analysis. All tests of statistical significance will be interpreted with a criterion of *P* < 0.05, two-sided.

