One phenotype that has a high prevalence rate in clinical populations and that elicits considerable problems with emotional regulation, depression, and circadian disturbances is severe mood dysregulation (SMD). Children and adolescents with SMD show severe affective and behavioral dysregulation, including irritable mood, hyperarousal, and increased reactivity to negative emotional stimuli [31,32]. Characteristics of SMD include not only depressive symptoms that might develop into MDD later on [33], but also circadian dysfunctions such as reduced need for sleep, disturbances in sleep continuity at sleep onset and through the night, lower sleep efficiency, reduced rapid eye-movement (REM) sleep and impaired daytime behavior, which have consistently been reported [34-36]. The initial treatment approaches, similar to those for pediatric bipolar disorder and attention deficit hyperactivity disorder (ADHD), include mood stabilizers and stimulants, and have shown some positive effects [37,38]. A novel psychosocial treatment with CBT indicated improvements in depressive symptoms, mood lability, and global functioning [39]. Although these initial treatment approaches were reported to have some positive effects on SMD symptoms, children and adolescents with SMD and additional ADHD were more likely to remain significantly impaired than those with only ADHD after a 3-week combination trial with stimulants and behavior modification therapy [37]. Therefore, a wider range of treatment approaches for SMD is needed, as those that have been evaluated to date have shown only limited improvements. It is possible that, as in juvenile depression, circadian disturbances might be an influencing factor on treatment outcome in SMD. Considering that preliminary results of light application besides SAD and MDD have shown positive influences on affective and behavioral regulation and on circadian functioning, light therapy might constitute a reasonable co-treatment for SMD symptoms as well [40].

The proposed study is an RCT of bright-light therapy in juvenile depression. We plan to enroll 60 adolescents with depression. We hypothesize that 2 weeks of morning bright-light therapy will improve depressive symptoms and additional sleep disturbances in these adolescents. On an exploratory basis, the study will additionally evaluate the outcomes of morning light therapy on SMD symptoms.

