### Primary and secondary endpoints

The primary endpoint of the study is the change in depression symptoms (BDI-II total score) during the trial. Secondary endpoints include changes in general psychopathology, sleep, circadian functioning (including melatonin assessment), affective dysregulation, behavior, and attention parameters. All questionnaires will be presented in German, and will be completed within the hospital.

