#### Time points of assessments

The assessment time points are as follows.

•T1: The initial assessment for eligible patients will be carried out after about 1 week of care in the unit. At this point, patients will have become used to being in the hospital, and will probably have a more regular day and night rhythm.

•T2: After 2 weeks of morning light-therapy intervention, there will be a comprehensive post-therapy assessment.

•T3: One week later, depression severity will be assessed to monitor changes.

•T4: Another week later, there will be another assessment of depression severity.

•T5: Three weeks after the light-therapy interventions have ended, another comprehensive assessment will be carried out.

An overview of the timeline of the study is shown in Figure 2.

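### The primary BDI-II endpoint names no deciding visit or model term, tests T2 to T5 at an unadjusted 5%, and names only pre-post effect sizes

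*Protocol article*

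**What the plan says.** The section Primary and secondary endpoints states: "The primary endpoint of the study is the change in depression symptoms (BDI-II total score) during the trial". The Statistical analyses section repeats this definition without adding a visit.

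The visits answer different questions. Time points of assessments has "T2: After 2 weeks of morning light-therapy intervention, there will be a comprehensive post-therapy assessment" and "T5: Three weeks after the light-therapy interventions have ended, another comprehensive assessment will be carried out"; T3 and T4 fall one and two weeks after T2. The Background hypothesis, "We hypothesize that 2 weeks of morning bright-light therapy will improve depressive symptoms", points towards the end of treatment but ties success to no visit.

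On analysis, the Statistical analyses section says "All planned comparisons will compare T2 to T5 relative to T1". The model is given as follows: "two-factor repeated-measures ANCOVA will be used with group as between-subject factor and time as within-subject factor (T1 to T5"). Baseline BDI-II "will be controlled for in the two-factor repeated-measures ANCOVA". Every significance test is read at P < 0.05, two-sided, and no multiplicity rule is given. On effect measures: "The 95% confidence intervals and pre-post effect sizes will be derived for each analysis".

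**The concern.** A two-factor repeated-measures ANCOVA with four follow-up visits yields several group-related results: a group effect, a group-by-time interaction, and a group contrast at each of T2, T3, T4 and T5. The article does not say which one answers the primary question. A significant T2 difference that has gone by T5, a T5 difference absent at T2, or a significant interaction could each be reported as primary success without departing from the text. If the choice is made after the results are seen, the 5% error rate no longer describes the primary claim.

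The second issue is the measure of size. The only effect size named is a pre-post one. Both arms receive usual inpatient treatment (Interventions), and the article expects relatively high placebo effects (Control group; Therapy expectancy). Patients are also selected for moderate to severe depression, so some regression to the mean is likely. A within-arm pre-post effect size would include all of these.

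**Working it through.** **1. The plan's own figure.** Inputs from Sample-size calculation: effect size 0.78, two-sided alpha 0.05, power 80%, total N 54. From Control group: half the patients are allocated to each arm.

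- Normal approximation per arm: n = 2(1.960 + 0.842)² / d² = 2 × 7.85 / 0.78² = 15.70 / 0.608 = 25.8, so 26 per arm, total 52.
- Two-sample t-test (noncentral t): 26.8, so 27 per arm, **total 54**, which matches.
- Alternatives that do not give 54: a paired test at 0.78 (15 patients), a one-sided two-sample test at 0.78 (total 44), and 0.53 as the between-group difference (total 112 normal, 114 t).

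So 54 is the size for one two-group comparison, with no allowance for several.

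**2. Error rate if any of T2-T5 may count (an assumed decision rule).**

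- Independent tests: 1 − 0.95⁴ = 0.185.
- Correlated tests, simulated with 30 per arm: 17.4% at correlation 0.3, 15.7% at 0.5, 13.2% at 0.7, 11.3% at 0.8, 9.1% at 0.9.

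The article gives no between-visit correlation for these patients. Its only related figure is a retest reliability of at least 0.75 in a non-clinical population, so all correlations here are assumptions. The relevant correlation is the one left after baseline adjustment, which is lower than the raw one. With correlation b between baseline and each follow-up visit and f among follow-up visits, it is (f − b²)/(1 − b²). For b = f = 0.7 this is (0.70 − 0.49)/(1 − 0.49) = 0.41. For b = 0.4, f = 0.8 it is (0.80 − 0.16)/(1 − 0.16) = 0.76.

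Baseline-adjusted simulation, 30 per arm, 8,000 runs per structure:

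| Assumed structure | Any of T2-T5 at 5% |
|---|---|
| Equal correlation 0.5 | 17.4% |
| Equal correlation 0.7 | 16.3% |
| AR(1), 0.7 | 15.1% |
| Baseline 0.5, follow-up 0.75 | 13.4% |
| Baseline 0.4, follow-up 0.8 | 12.5% |

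A single T2 contrast, or the group effect averaged over T2-T5, stays at about 5% in the same structures.

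**3. The model term matters too.** The group-by-time interaction over T1-T5 has (2 − 1)(5 − 1) = 4 degrees of freedom; the group effect has 1. Because T1 is both a covariate and a level of time, the covariate explains T1 completely. The group test over T1-T5 is therefore the same test as the group effect averaged over T2-T5. If the group and interaction tests were both read at 5% and treated as independent, the chance of at least one false positive would be 1 − 0.95² = 9.75%.

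**4. Power of the two candidate single contrasts** (30 per arm, the same five structures, effect in SD units):

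| Assumed effect at T2, T3, T4, T5 | T2 alone | T2-T5 average |
|---|---|---|
| 0.53 throughout | about 59-81% | about 67-97% |
| 0.53, 0.4, 0.3, 0.2 | about 58-81% | about 36-72% |

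The 0.53 is the article's non-seasonal figure. The fading profile is invented for illustration; the article gives none.

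**5. Keeping all four as primary.** Bonferroni uses 0.05/4 = 0.0125 per contrast. At d = 0.78, power per contrast is 61% with N = 54 and 67% with N = 60. Reaching 80% needs N = 78 (t-test).

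**6. Pre-post effect size.** Suppose both arms improve by 0.78 SD. Each within-arm pre-post size is 0.78, and the between-arm effect is 0.78 − 0.78 = 0.

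**The case against.** Four objections deserve an answer.

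- **No any-one-wins rule is written.** The sentence on T2 to T5 fits contrasts inside one model. A reader might infer that the trial gives itself four chances of success, but the documents do not say so. This stands: 12-17% is the cost of one permitted reading, not a property of the stated plan.
- **The inference is randomised.** A reader might conclude that the trial drops its control group and tests change within the active arm. The documents do not support that, because group is the between-subject factor and baseline is adjusted for. In the example with equal improvement in both arms, the group test would have no real difference to find. Nor does any passage make the pre-post size the headline result. The label itself is loosely used: the sample-size section calls its 0.78 pre-post, yet 54 comes out only when 0.78 is treated as a between-group difference. So within arm is the natural reading of the label but not a certain one.
- **Power need not suffer.** The named model offers a 1-df group effect with about 5% error, and with a sustained effect it is more powerful than T2 alone. A general claim of lost power would rest on an assumed fading profile.
- **This is a condensed article about a pilot, and an analysis plan may settle the matter.** That would excuse silence. Here, however, the article does state the primary endpoint, comparisons, model, alpha and effect measure, and as stated they admit several primary results. The pilot label is limited cover, since the article states an efficacy hypothesis, an 80% power calculation and significance tests.

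**Conclusion.** The point holds in this form: the protocol article does not fix which visit or model term decides the primary BDI-II endpoint, states no multiplicity rule for T2-T5, and names pre-post rather than between-group effect sizes.

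The size is conditional. If any one of the four baseline-adjusted comparisons could count, the false-positive risk is about 12-17% under the five assumed correlation structures, or 9-18.5% over the wider range from test correlation 0.9 to independence. If one contrast is fixed in advance, it is about 5%. The sample size supports one comparison only.

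The effect-measure problem is confined to reporting. It arises if pre-post means within arm, and it does not affect the validity of the planned group test.

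**What to change.** In Primary and secondary endpoints and in Statistical analyses, name one primary contrast before any outcome is analysed by allocated group: the baseline-adjusted active-minus-control difference in BDI-II, tested two-sided at 5%, reported with its 95% CI and a between-group standardised difference. Two choices are defensible:

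- **T2**, the end of treatment, which matches the two-week hypothesis.
- **The average over T2-T5**, which matches a definition covering the whole trial.

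Make the remaining visit-wise comparisons and the interaction secondary, without confirmatory claims. Keep pre-post effect sizes as descriptive figures for each arm.

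The cost is wording only, with no extra patients or visits. The remaining visits can no longer be claimed as primary success. T2 alone gives up power relative to the average if the effect is sustained and gains power if it fades, so the choice should reflect the question the trial wants answered.

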##### Seasonal pattern assessment questionnaire

The Seasonal Pattern Assessment Questionnaire (SPAQ) is a questionnaire for retrospectively assessing change in mood and vegetative functions with the seasons [69]. It is a frequently used screening instrument for assessing symptoms of SAD, with a high internal consistency [70] and has recently been used in young adults [71]. In the present study it will be administered to calculate a total seasonality score, with seasonality being the degree to which seasonal changes affect criteria such as mood, energy, sleep length, appetite, food preference, or the wish to socialize with other people [69], and thus will be used to control for seasonal effects.

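### The article both fixes baseline BDI-II in the primary model and makes it conditional on a significance test against the outcome, so the primary covariate set is not prespecified

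*Protocol article*

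**What the plan says.** All of the following is in the protocol article, under Data analysis, Statistical analyses, unless stated otherwise.

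- Endpoint: "The primary endpoint of the study is change in depressive symptoms (BDI-II total score) during the trial".
- Baseline, unconditional: "Baseline depression level (that is, BDI-II total score at T1) will be controlled for in the two-factor repeated-measures ANCOVA". The next sentence gives the purpose: "This model accounts for differences between groups at baseline".
- Covariates, conditional: "In cases of significant correlations with the primary endpoint, covariates will include baseline BDI-II score, gender, intelligence, seasonality, and circadian preference". Baseline BDI-II is the first of the five items that the condition governs.
- Model: "two-factor repeated-measures ANCOVA will be used with group as between-subject factor and time as within-subject factor (T1 to T5").
- Missing data: multiple imputation, with "Each of the datasets is then analyzed separately using the desired model (in this case, the two-factor repeated-measures ANCOVA"), after which the estimates are combined by standard rules.
- Threshold for tests: "All tests of statistical significance will be interpreted with a criterion of *P* < 0.05, two-sided".

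The section on the Seasonal Pattern Assessment Questionnaire (SPAQ) says that its total seasonality score "thus will be used to control for seasonal effects".

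**The concern.** The two sentences on baseline BDI-II cannot both apply as written. If the first governs, baseline is always in the model. If the second governs, baseline stays only when it passes a test against the outcome, and the claim that the model deals with baseline group differences is no longer assured.

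The other four covariates (gender, intelligence, seasonality, circadian preference) are conditional under any reading. Their entry is decided by significance against the trial's own endpoint, after outcomes are known. The rule leaves open whether the screen uses the score or the change, and which of the visits T2 to T5. It could also return different covariate sets in different imputed datasets, although the imputation text presumes one common model.

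At stake is whether the primary p-value comes from a model fixed beforehand or from one that the data, or an analyst's reading of the rule, has selected.

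**Working it through.** **1. The plan's own figure.** The only number in the analysis plan that can be reproduced is the total of 54. A two-sample t-test with d = 0.78, two-sided α = 0.05 and 80% power needs 26.8 per arm, so 27 per arm and 2 × 27 = 54. No covariate or baseline correlation enters this calculation, so it neither supports nor settles the covariate rule.

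**2. Number of possible models.** Five covariates, each in or out: 2⁵ = 32 sets. With baseline fixed, four remain: 2⁴ = 16.

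**3. What the screen requires.** For n = 60, the planned enrolment, the critical correlation at two-sided 0.05 is t/√(58 + t²). With t = 2.002 this is 2.002/√(58 + 4.007) = 0.254.

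**4. How often baseline would fail the screen.** The pre-post correlation r is not in the article, so a range is assumed. With equal variances, baseline correlates r with the later score but −√((1 − r)/2) with change. At r = 0.3, 0.5 and 0.7 the latter is −0.59, −0.50 and −0.39, all beyond 0.254 in size. The measure screened therefore matters a great deal. Simulated share of trials in which baseline is dropped (60 patients, 1:1, one post-baseline visit):

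| r | Screened against change, d = 0.53 | Screened against score, no effect |
|---|---|---|
| 0.2 | 0.04% | 67% |
| 0.3 | 0.06% | about 35% |
| 0.4 | 0.6% | 11% |
| 0.5 | 2.0% | about 2% |
| 0.7 | 17% | 0% |

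The endpoint is defined as change, so the change column is the natural reading.

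**5. Effect on power.** Baseline always included versus the rule, at d = 0.53, the non-seasonal effect quoted under Sample-size calculation:

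- Change: 55.4% vs 55.4% (r = 0.3), 63.7% vs 63.5% (r = 0.5), 79.5% vs 78.8% (r = 0.7).
- Score: 52.8% vs 51.9% (r = 0.2), 55.3% vs 54.4% (r = 0.3), 59.4% vs 58.6% (r = 0.4), 63.8% vs 63.7% (r = 0.5).

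The largest difference is 0.9 points. In the score screen, baseline is dropped mainly when r is low, and then adjustment would have gained little.

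**6. Effect on type I error.** Simulated with four further independent covariates (coefficient 0.2 each, assumed), screening against change, 4000 runs per setting: 4.9% to 5.7% under the rule, against 5.0% to 6.0% with baseline always included. The simulation standard error is √(0.05 × 0.95/4000) = 0.34 points, so there is no material inflation.

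**7. Room for choice.** A worst-case simulation fixed the outcome as mean change over four visits (inter-visit correlation 0.6 and covariate coefficients 0.2, both assumed). It varied only what the text leaves open: the visit or average screened, score or change, and baseline fixed or conditional. On average 4.5 to 6.1 distinct models were permitted per trial. Reporting the most favourable one each time gave a type I error of 8.3% to 11.5%. This shows what the wording fails to exclude; it does not predict what the investigators would do.

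**The case against.** The strongest reply is that this is loose drafting. The unconditional sentence is explicit, so baseline is fixed and the condition was meant for the other four covariates. That is plausible, and it reduces 32 sets to 16. But the conditional sentence names baseline first in its list, and even on this reading the outcome still selects among the other four.

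A second reply is that a condensed article of a self-described pilot may leave the visit screened and the handling of imputed datasets to a fuller document. That stands: those details are not faulted as missing. The selection rule itself is stated, however, and it is the rule that is badly fixed.

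Four stronger readings are tempting, and the documents do not support them:

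- **A large power loss.** Power at d = 0.53 and r = 0.5 is 52% without baseline and 63% to 65% with it. That contrast compares never adjusting with always adjusting, which is not the plan's rule. At r = 0.5 the rule keeps baseline in about 98% of trials.
- **Baseline lost altogether if dropped.** T1 is a level of the time factor and comparisons are relative to T1, so baseline still enters through change. What is lost is its role as a covariate.
- **Imputed datasets that cannot be pooled.** Nothing says that selection is made separately in each dataset, and the text speaks of a single model. Even if covariate sets differed, each model would yield a group estimate and standard error. The fair statement is that the combining rules presume one common model and the screen does not guarantee it.
- **A contradiction with the SPAQ section.** That section gives the general purpose of the questionnaire. Making seasonality conditional later is a mild tension only.

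**Conclusion.** The point holds as a self-contradiction on baseline BDI-II and as an outcome-driven rule for the primary covariate set. Its size is modest. Applied mechanically, with screen and outcome on the same measure, the rule leaves type I error near 5% and costs about 1 point of power or less. With change as the screened endpoint, baseline is dropped in about 2% of trials or fewer for r up to 0.5, and in 17% at r = 0.7. The harm is the loss of a prespecified primary model and the freedom this leaves over the primary p-value.

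These figures assume 60 patients allocated 1:1, a single post-baseline visit and pre-post correlations of 0.2 to 0.7. They do not cover screening on one measure while analysing another. The 8.3% to 11.5% in step 7 further requires that the most favourable model be picked every time, and nothing in the article suggests that it would be. The textual contradiction depends on none of these assumptions. The change should be made before the data are analysed.

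**What to change.** Delete the significance condition. State that baseline BDI-II is in the primary model unconditionally. Name any further covariates now, on prognostic grounds (for example gender and the SPAQ seasonality score), and use the same set in every imputed dataset. Use the remaining candidates only in a stated sensitivity analysis.

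The cost is one sentence, plus at most a degree of freedom or two if a named covariate proves uninformative. The article lists the trial as ongoing, so the change can still precede the analysis.

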##### Sleep questionnaire B - revised

Sleep and sleep difficulties will be assessed by using the Sleep Questionnaire (Schlaffragebogen) B - Revised (SF B/R) described by Görtelmeyer *et al*. [52]. This questionnaire contains 31 questions, assessing the 2 weeks prior to assessment. Completion takes about 5 to 10 minutes, and 11 sleep indices can be created including: difficulties in sleep onset and in sleeping through the night, premature awakening, general sleep characteristics, total sleep duration, and sleep factors consisting of sleep quality, feeling of recovery after sleeping, mental balance before going to sleep, feeling of mental exhaustion before going to sleep, and psychosomatic symptoms during sleep phase. Internal consistency is moderate to excellent (α coefficient = 0.68 to 0.92) for clinical populations. Test-retest reliability indicates that relatively stable sleep-related behavior and experiences can be assessed (r = 0.53 to r = 0.91).

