### Data analysis

#### Sample-size calculation

Estimates of a clinically relevant effect size were derived from a meta-analysis that evaluated effects of bright-light therapy for seasonal and non-seasonal depression in adult outpatients [74]. A similar study for adolescent inpatients is not available. Therefore, effect-size calculation will be based on evidence from adult outpatients. Although research is generally scarce, it is assumed that the active light therapy intervention for SAD will have an effect size (pre-post) of about 0.78 [75], which can be considered a conservative estimate because effect sizes might be considerably higher [74]. Golden *et al*. [74] divided the studies used in their meta-analysis into four categories, and derived effect sizes for them. In the category ‘non-seasonal depression’, an effect size of 0.53 was reported for bright-light treatment, with a 95% confidence interval of 0.18 to 0.89. Conservative calculations indicate that the expected outcome for our study will require a total sample size of 54 subjects (α = 0.05, two-sided test) to achieve a power of 80%.

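### If the stated T1-relative model is used for the secondary endpoints, sleep, behaviour, melatonin onset and attention are compared without adjustment for their own T1 values, which costs precision

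*Protocol article*

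**What the plan says.** All references are to the protocol article.

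- **Hypothesis (Background).** The trial expects that "2 weeks of morning bright-light therapy will improve depressive symptoms and additional sleep disturbances in these adolescents". Only the severe mood dysregulation question is called exploratory.
- **Endpoints (Primary and secondary endpoints).** The primary endpoint is change in the BDI-II total score. "Secondary endpoints include changes in general psychopathology, sleep, circadian functioning (including melatonin assessment), affective dysregulation, behavior, and attention parameters".
- **Reference point (Statistical analyses).** "All planned comparisons will compare T2 to T5 relative to T1".
- **Model (same section).** A two-factor repeated-measures ANCOVA is named for the trial, with group between subjects and time within subjects, T1 to T5. No other between-group model is given.
- **Covariates (same section).** T1 BDI-II is to be controlled for, and the section says that the model thereby deals with baseline differences between the arms. Subject to a significant correlation with the primary endpoint, "covariates will include baseline BDI-II score, gender, intelligence, seasonality, and circadian preference".
- **Availability of T1 values.** The Abstract places the test battery before treatment, after treatment and three weeks later. The DLMO section places saliva sampling at T1, T2 and T5.

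**The concern.** When T1 is the first level of the time factor, a group-by-time contrast against T1 is a difference between arms in change scores. For sleep, SDQ, CGI-S, DLMO or attention, nothing in the covariate list supplies that endpoint's own T1 value. Baseline BDI-II measures depression and cannot account for a baseline difference in sleep or reaction time. The entry rule for covariates also looks at correlation with the primary endpoint, not with the endpoint being analysed.

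The stake is precision. Sleep shares the stated hypothesis with depression, and the trial has about 30 patients per arm. The Randomization and blinding section describes a simple draw with no stratification, so chance T1 differences between arms are to be expected. A change score carries part of such a difference into the estimate, and adjustment for the endpoint's own T1 value removes it on average.

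**Working it through.** **Inputs from the protocol article**
- N = 60 (Abstract, Background), equal allocation (Randomization and blinding), two-sided 0.05 (Statistical analyses).
- Effect for non-seasonal depression 0.53, 95% CI 0.18 to 0.89 (Sample-size calculation). It is for depression and is borrowed here, because no effect size is given for any secondary endpoint.
- Retest correlation 0.53 to 0.91 for the sleep questionnaire and 0.62 for the SDQ (their sections under Assessments). The section on the attention tests gives internal consistency only (0.60 to 0.83).

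**The plan's own figure.** The article says that the expected outcome "will require a total sample size of 54 subjects" for 80% power. A two-sample t-test with exact noncentral-t power gives 54 in total at d = 0.78 and 114 at d = 0.53. So 54 is reproduced with 0.78 used as a between-group effect. It concerns depression; no power is stated for a secondary endpoint.

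**Variances.** Take SD 1 at each time point, pre-post correlation r, and one post-treatment time point against T1.
- Change score: 2(1−r)
- ANCOVA on the endpoint's own T1 value: 1−r²
- Ratio of ANCOVA to change score: (1−r²) / [2(1−r)] = (1+r)/2

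Multiplying the ratio by 60 gives the number of patients at which own-baseline ANCOVA would match the precision of the change score in all 60. This needs no effect size.

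| r | Change SD | ANCOVA SD | Ratio | 60 × ratio |
|---|---|---|---|---|
| 0.53 | 0.970 | 0.848 | 0.765 | 45.9 |
| 0.62 | 0.872 | 0.785 | 0.810 | 48.6 |
| 0.75 | 0.707 | 0.661 | 0.875 | 52.5 |
| 0.91 | 0.424 | 0.415 | 0.955 | 57.3 |

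The value 0.75 is an intermediate point within the sleep questionnaire's range.

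**Power at N = 60.** Noncentrality is (d / SD) × √15. At r = 0.53 and d = 0.53 this is 0.547 × 3.873 = 2.12 for change and 0.625 × 3.873 = 2.42 for ANCOVA.

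| r | d = 0.53: change / ANCOVA | Loss | d = 0.78: change / ANCOVA | Loss |
|---|---|---|---|---|
| 0.53 | 54.9% / 66.3% | 11.4 | 86.5% / 93.8% | 7.3 |
| 0.62 | 63.9% / 73.0% | 9.1 | 92.6% / 96.6% | 4.0 |
| 0.75 | 81.4% / 86.2% | 4.8 | 98.7% / 99.4% | 0.7 |
| 0.91 | 99.7% / 99.8% | 0.1 | 100.0% / 100.0% | 0.0 |

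**Without a borrowed effect.** The small losses at high r partly reflect power already near 100%. If own-baseline ANCOVA is set at 80% power, the change score has 68.8% (r = 0.53), 71.3% (0.62), 74.6% (0.75) and 78.2% (0.91). The losses are 11.2, 8.7, 5.4 and 1.8 points.

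**Does the BDI-II covariate recover the loss?** If T1 BDI-II correlates equally with the endpoint before and after treatment, it is uncorrelated with the change and removes none of its variance. Simulation with an assumed correlation of 0.3 and d = 0.53 at N = 60 leaves a gap of about 11 points at r = 0.53 and 7 to 9 points at r = 0.62.

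**Baseline imbalance.** The chance T1 difference between arms has SD √(2/30) = 0.26. The change score carries (1−r) of it: 0.47 × 0.26 = 0.12 SD at r = 0.53. The excess variance of the change score is 2(1−r) − (1−r²) = (1−r)², which is this same term. Imbalance therefore explains the loss above and adds no second one.

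**The case against.** The strongest reply is that the article never says which model or covariates apply to the secondary endpoints. The text around the model is about the BDI-II, and the covariate sentence is conditional on correlation with the primary endpoint. A five-level time factor fits only the BDI-II schedule: Time points of assessments gives T3 and T4 to depression severity alone, and DLMO is sampled only at T1, T2 and T5. On this reading the secondary model is unstated and may stand in an analysis plan that is not shown.

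Much of this stands. A reader might infer that the protocol commits to analysing sleep, behaviour and attention as unadjusted change. It does not say so, and applying the stated model to these endpoints is an inference. But the T1-relative rule covers all planned comparisons, the secondary endpoints are defined as changes, and no other between-group model is offered. Followed as written, that fixes a change-from-T1 comparison, and nothing in the article adds the endpoint's own T1 value.

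It is also fair to say that a change-score contrast is unbiased under randomisation, that this is a pilot, and that a general loss of 9 to 11 points would overstate the case. That figure needs r of about 0.53 to 0.62 and the borrowed effect of 0.53. The sleep questionnaire's own range reaches 0.91, and for the attention tests there is no retest value to work from.

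**Conclusion.** The point holds conditionally. If the stated model is applied to the secondary endpoints, they are compared as change from T1 without adjustment for their own T1 values, and baseline BDI-II is no substitute. The cost is efficiency, not validity. The power loss is up to about 11 points at the lowest sleep-questionnaire correlation and about 9 at the SDQ value, falling to about 5 at 0.75 and almost none at 0.91.

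These figures assume that retest reliability stands in for the pre-post correlation under treatment, that SDs are equal over time, that the depression effect of 0.53 SD applies to these scales, and that a single post-treatment time point is compared with T1. For attention no figure can be tied to the document.

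Two stronger readings are not supported. The documents do not show bias: a distorted estimate arises only conditionally on an observed T1 imbalance. Nor do they show that the BDI-II is the only baseline covariate: intelligence, seasonality and circadian preference are listed too, but none is the T1 value of the sleep questionnaire, SDQ, CGI-S, DLMO or attention tests.

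**What to change.** Add one sentence to Statistical analyses, along these lines:

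> For each secondary endpoint measured at T1 (SF B/R, SDQ, CGI-S, DLMO, TAP), the values after randomisation are the outcome, and that endpoint's own T1 value is always included as a covariate, in place of baseline BDI-II and regardless of its correlation with the primary endpoint.

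T1 must then leave the time factor for these endpoints, since it cannot be both outcome and covariate. CGI-I rates improvement, has no T1 value, and is analysed without one. If an analysis plan already says this, a reference to it is enough.

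The T1 values are already part of the planned assessments, so no patients, visits or measurements are added. The cost is at most one degree of freedom per model, and none net where the own T1 value replaces baseline BDI-II.
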